
### Sample Size Calculation

Data on AKI-occurrence in a cohort of 83 patients, treated at Princess Máxima Center for a renal tumor in the period 2015-2018, was used for our sample size calculation. In this retrospective cohort, AKI after surgery occurred in approximately 37.1% of patients. Power analysis for a one-sample proportion test was applied to compute the number of patients required for this study (72). The statistical program G^*^Power, version 3.1, was used to compute the sample size. To detect a change in proportion from 37 to 18% with 80% power, using a 5%-level two-sided test, 50 patients are needed.

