### Randomization

The computer program Castor EDC (Amsterdam, the Netherlands), used in compliance with laws and regulations, will be used to randomize study subjects after acquiring informed consent. Randomization will be performed in a 1:1 ratio with stratification for age-group and sex. Due to the nature of our intervention, subjects and investigators cannot be blinded to the result of randomization.

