### Statistical Analysis

Statistics will be computed using IBM SPSS software version 25.0 (Chicago, IL, USA) or R version 4.0.3 or newer. An intention-to-treat analysis will be conducted to account for the feasibility of the diet. A two-sided significance level of 0.05 will be used for all primary and secondary analyses unless stated otherwise. An analysis will be performed with multiple imputation in the case of missing data. All preoperative / baseline characteristics will be described for the intervention group and the control group. To determine the primary endpoint, we will calculate the proportion of AKI present on postoperative day three after radical nephrectomy in the two treatment arms. Results will be compared by using a Chi-square test for 2 proportions.

In the secondary analysis, a multivariable logistic regression model will be estimated to study the treatment effect of fasting on the occurrence of AKI, adjusted for confounders such as age, sex, weight and compliance to the diet. Additionally, a multinominal logistic regression model will be estimated to investigate the treatment effect of fasting on the substages of AKI. Proportions of substages of AKI will be compared by using the Chi-square test for equality of proportions generalized to more than two independent samples. Due to the presence of repeated measurements, mixed models will be estimated for the following outcomes: postoperative renal function, postoperative renal tissue injury, change in physical activity, quality of life and body weight, to investigate the effect of STF. Confounders such as age, sex, and an interaction term between time and group will be incorporated in each mixed model. Adherence to the diet and occurrence of side effects will be reported as percentage. Change in metabolic, endocrine, and fasting parameters, clinical parameters of mobilization, duration of in-patient hospitalization, occurrence and duration of ICU admission, physiotherapy assessment, occurrence of perioperative complications and upregulation of cytoprotective genes and inflammatory markers will be compared between the two treatment groups by using the *t*-test in the case of continuous outcome variables or non-parametric test in case of violations of normality assumption. The Chi-square test will be used for categorical data.

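### The 50 patients and 80% power come from a one-sample test; under the planned 1:1 two-arm chi-square comparison, 50 patients in total give about 32–34% power

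*Protocol article*

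**What the plan says.** The Sample Size Calculation section starts from a retrospective cohort of 83 patients at the same centre, in which "AKI after surgery occurred in approximately 37.1% of patients". It then names the method, "Power analysis for a one-sample proportion test was applied to compute the number of patients required for this study", and gives the result: "To detect a change in proportion from 37 to 18% with 80% power, using a 5%-level two-sided test, 50 patients are needed".

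The design and the analysis are fixed elsewhere in the article. Under Randomization: "Randomization will be performed in a 1:1 ratio with stratification for age-group and sex". Under Statistical Analysis, for the primary endpoint, "we will calculate the proportion of AKI present on postoperative day three after radical nephrectomy in the two treatment arms", followed by "Results will be compared by using a Chi-square test for 2 proportions". The same section sets the error rate: "A two-sided significance level of 0.05 will be used for all primary and secondary analyses unless stated otherwise".

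No section plans a comparison of one arm, or of all patients, with a fixed historical rate.

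**The concern.** The sample size model and the trial do not match. A one-sample test asks whether a single group of 50 differs from a rate known without error. The trial asks whether two concurrent groups differ from each other. This changes two things. Only half of the patients receive the intervention, and the control rate has to be estimated from the other half, with its own sampling error. Both reduce power, and the one-sample formula allows for neither.

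What is at stake is how the primary result is read. The article sets out to determine the effect of fasting on AKI. Someone who relies on the stated 80% would take a non-significant chi-square test as fairly strong evidence against the assumed effect. If power is far lower, the same result says little either way.

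**Working it through.** **Inputs.** p0 = 0.37 and p1 = 0.18, two-sided alpha 0.05 (z = 1.960), power 0.80 (z = 0.8416) and 50 patients, all from Sample Size Calculation; 1:1 allocation from Randomization; chi-square test for two proportions from Statistical Analysis. Then p0(1 − p0) = 0.2331, p1(1 − p1) = 0.1476 and p0 − p1 = 0.19.

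**Step 1: reproduce the plan's figure.** One-sample formula:

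n = [(1.960·√0.2331 + 0.8416·√0.1476) / 0.19]² = [(0.9463 + 0.3233) / 0.19]² = 44.7.

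With the usual continuity correction, n' = (n/4)·[1 + √(1 + 2/(n·0.19))]² = 49.8, which rounds up to 50. The exact two-sided binomial test against 37% has 82.3% power at n = 50. So 50 is reproduced as a one-sample figure, and as such its arithmetic is sound. The two-sample variants tried do not give 50, in total or per arm: 86 per arm two-sided, 68 per arm one-sided, 96 per arm two-sided with continuity correction.

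**Step 2: power of the planned test with 25 per arm.** The pooled proportion is (0.37 + 0.18)/2 = 0.275, and 2·0.275·0.725 = 0.39875. The sum of the two variances is 0.2331 + 0.1476 = 0.3807.

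Power = Φ[(0.19 − 1.960·√(0.39875/25)) / √(0.3807/25)] = Φ[(0.19 − 0.2475)/0.1234] = Φ(−0.466) = 32.1%.

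Other methods at 25 per arm:

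| Method | Power |
|---|---|
| Pooled normal approximation | 32.1% |
| Arcsine approximation | 33.2% |
| Exact enumeration, uncorrected chi-square | 33.7% |
| Exact enumeration, Yates correction or Fisher's exact test | about 21% |

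Using 37.1% in place of 37% gives 32.3% (normal) and 34.0% (exact), so rounding the cohort rate does not matter.

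**Step 3: the other reading of 50.** With 50 per arm, the normal approximation gives Φ[(0.19 − 0.1750)/0.0873] = 56.8%, and exact enumeration gives 57.6%.

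**Step 4: size needed for 80%.** n per arm = [(1.960·√0.39875 + 0.8416·√0.3807) / 0.19]² = [(1.2377 + 0.5193)/0.19]² = 85.5, so 86 per arm, 172 in total. By exact enumeration 85 per arm suffices (80.4%).

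**Step 5: what 25 per arm can detect.** With a control rate of 37%, 80% power needs a fasting-arm rate of about 5.4% by the normal approximation or about 6.5% by exact enumeration (80.5%). At 7% the exact power is 78.5%.

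**Step 6: precision.** The expected 95% CI half-width for the risk difference is 1.960·√(0.3807/25) = 1.960·0.1234 = 0.242, about 24 percentage points, which is wider than the 19-point target difference. Two examples near the assumed rates, by the uncorrected chi-square test: 9/25 against 5/25 gives p = 0.21, and 9/25 against 4/25 gives p = 0.11.

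**The case against.** **The one-sample arithmetic is right.** True: the inputs lead to about 50. The fault lies in applying that model to a trial with a different design and test.

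**The text does not say whether 50 is the total or per arm.** Also true, and the power figure should carry that qualification. The section speaks of the number required for the study, which favours the total. The other reading still leaves power near 57–58%, so the 80% claim fails on both.

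**Another analysis might rescue the figure.** It does not. A one-sided test with 25 per arm has about 44% power, and the article says two-sided. Testing 25 fasting children against a fixed 37% would have about 52% (exact binomial), and no such test is planned. The covariate-adjusted logistic model is a secondary analysis.

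**An article condenses the protocol.** That excuses omissions. Here the method, inputs and result are all stated, and they conflict with the stated design. No separate analysis plan could give 25 per arm 80% power under this chi-square test.

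Two stronger readings are tempting, and the documents support neither:

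- A reader might infer that a null result would most likely be a false negative. Power gives the chance of non-significance if the rates really are 37% and 18%. The chance that an effect exists given a null result also depends on how plausible the effect was beforehand, which the article does not quantify.
- A reader might infer that the ethics committee and families were given a wrong power figure. The Ethics and Dissemination section says that the committee approved the study protocol, which is not shown. Nothing in the article shows what power figure, if any, families were told.

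**Conclusion.** Wrong as written. The stated 80% power belongs to a one-sample test that the trial does not perform. For the planned two-sided 5% chi-square comparison of 37% with 18%, power is about 32–34% if 50 is the total and about 57–58% if 50 is per arm. About 85–86 per arm, roughly 172 in total, would be needed for 80%.

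On the reading as a total, the primary test would miss the assumed effect about two times in three. A non-significant result should therefore not be taken as evidence that fasting has no effect on AKI.

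These figures assume the plan's own rates, equal arms, an uncorrected chi-square test and no loss of patients. A continuity correction, Fisher's exact test or dropout would lower power further. The smallest detectable effect depends somewhat on the method of calculation, so it should be given as a range.

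**What to change.** Replace the calculation with a two-sample one that matches the 1:1 design and the primary chi-square test, and say whether 50 is the total or per arm. If it is the total, wording such as this would do:

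*With 25 patients per arm, the two-sided 5% chi-square test has about 34% power (exact enumeration) to detect 37% versus 18%. Power of 80% is reached only if the rate in the fasting arm falls to about 5–6.5%, depending on the method of calculation. The expected half-width of the 95% confidence interval for the risk difference is about 24 percentage points. A non-significant result will not be interpreted as evidence of no effect.*

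Report the risk difference with its 95% confidence interval alongside the chi-square test. If the sponsor wishes to keep the 80% claim for 37% versus 18%, the matching size is about 172 in total.

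Describing the trial as a pilot or estimation trial is optional. It would change the purpose given in the Introduction and Discussion, which is to determine the effect on AKI, and the correction does not depend on it.

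**Cost:** a less favourable stated power and an amendment submitted to the ethics committee. Restating the figure needs no extra patients and does not alter trial conduct.

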### Recruitment

Inclusion will take place during the 3rd and 4th week of the preoperative chemotherapy period. Eligible subjects will be identified by the principal investigator and/or their treating physician. The coordinating investigator will provide detailed information, both orally and in writing, about the aims, design, and the study procedures. The subject and their caregivers will be offered a reflection period of 1 week until their next outpatient clinic visit, at which the informed consent form will be signed.

### Randomization

The computer program Castor EDC (Amsterdam, the Netherlands), used in compliance with laws and regulations, will be used to randomize study subjects after acquiring informed consent. Randomization will be performed in a 1:1 ratio with stratification for age-group and sex. Due to the nature of our intervention, subjects and investigators cannot be blinded to the result of randomization.

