Following short-term injury and toxicity experienced by children with cancer, adult survivors of childhood cancer are at risk for long-term nephrotoxicity, i.e., renal dysfunction and high blood pressure (47–51). In limited studies available, an increased risk of severe renal impairment was identified in unilateral WT-survivors (50, 52, 53). In a follow-up study of unilateral WT-survivors, 21% had stage II chronic kidney disease (CKD) (50). In another study in WT-survivors, 53% developed stage II CKD and hypertension was noted in 40% (54). Hence, adult survivors with a solitary kidney have a high relative risk of developing (end-stage) renal disease and this is most likely due to reduced renal mass/eGFR-reserve (55, 56). Pediatric patients that had an episode of acute kidney injury (AKI) are at increased risk for developing chronic renal disease, including hypertension and end-stage renal disease (49, 57, 58). Postoperative AKI is also associated with increased morbidity and longer hospital stay and the magnitude of this risk depends on the severity of AKI (59, 60). STF could potentially reduce hyperfiltration and oxidative stress, specifically on the contralateral kidney, and might therefore lower the risk and extent of acute and late nephrotoxic effects.

To investigate whether STF reduces toxicity and postoperative renal damage, we aim to conduct a single-center, prospective, parallel-group, non-blinded, randomized controlled trial in pediatric patients with renal tumors. These children follow a strictly planned treatment schedule and are in a relatively well condition in comparison with other pediatric oncology patients. This allows implementation of the study-intervention, which can provide further knowledge on the effects of preoperative fasting in pediatric patients. The primary objective of our study is to determine the effect of STF on the occurrence of AKI after tumor-nephrectomy. This study will also further enhance insight into the mechanism and the effect of STF.

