### Study Procedures

Subjects will be assessed for blood glucose levels 2 h before the planned time of surgery. If a subject shows any symptoms suggestive of hypoglycaemia (somnolence, trembling, sweating, pale skin color, tachycardia, and/or irritability) during the fasting period, an additional point-of-care blood glucose test will be performed. Escape medication has been defined in the study protocol in the case of hypoglycaemia. For both treatment arms we standardized the induction of anesthesia, maintenance of anesthesia, postoperative pain relief, timing of surgery and IV-fluids for the first 24 h after surgery. General anesthesia will be induced and maintained with Sevoflurane. IV-fluid used during surgery is Kydialite (1% glucose), according to the estimated maintenance requirements following the 4/2/1 rule: 4 cc/kg/hr for the first 10 kg, 2 cc/kg/hr for the second 10 kg, and 1 cc/kg/hr for every kg above 20. It can be supplemented with Ringers lactate at the discretion of the anesthetic team. IV-Fluids during the 24 h after surgery are Ringer's lactate solution or equivalent, according to standard of care protocol (maintaining a diuresis of 1 cc/kg/hr).

Non-invasive interventions that will be conducted during study runtime are questionnaires to analyse aspects of wellbeing and the potential burden of the intervention, wearing an accelerometer and physiotherapeutic assessments. Subjective wellbeing will be analyzed using the PEDSQL-Cancer Module parent form (62, 63). Physiotherapeutic assessments will consist of a short questionnaire to gather information on physical functioning and strength [the SARC-F, (64)], measurements of (skeletal) muscle mass using leg circumference, ultrasonography of quadriceps muscles using a portable linear transducer [Philips Lumify, Philips N.V., Best, The Netherlands (65)] and body composition using bio-electrical Impedance Analysis [Bodystat, QuadScan 4000, Isle of Man, United Kingdom (66)]. Motor function will be evaluated using the Gross Motor Function Measure [GMFM-88 (67)]. Invasive procedures and study appointments will coincide with standard procedures to reduce the burden of participation. Tissue biopsies will be acquired from the removed kidney after diagnostic samples have been taken. Further details and an overview of all procedures are provided in the Appendix III: Study Workflow.

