### Primary Outcome

Our primary outcome is AKI on postoperative day 3, 48–72 h after surgery. AKI is defined according to the KDIGO-guidelines (68). The percentage of subjects developing AKI will be measured in both treatment arms. Laboratory measurement of serum creatinine (μmol/L) will be assessed by routine lab procedures and urine output (mL/kg/h) will be calculated by routine clinical procedures. eGFR will be automatically calculated using both the Chronic Kidney Disease Epidemiology Collaboration (CKD-EPI) formula and the Revised Schwartz Equation for Glomerular Filtration Rate (Schwartz-formula).

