### Secondary Outcomes

Our secondary endpoints comprise several aspects of the preoperative fasting diet and the postoperative recovery. All the secondary outcomes will be compared between the study arms to identify a possible influence of STF.

- The occurrence of the substages of AKI will be assessed on postoperative day 3. Substages are defined according to KDIGO guidelines (68). Laboratory measurement of creatinine (μmol/L) will be assessed by routine lab procedures and urine output (mL/kg/h) will be calculated by routine clinical procedures.- Postoperative renal function will be assessed using laboratory measurements, including creatinine (μmol/L), cystatin-C (mg/L), urea (mmol/L), albumin (g/L) and eGFR (ml/min), all assessed by routine lab procedures. These outcomes will be used to determine the postoperative recovery of renal function.– Renal tissue injury will be investigated on postoperative day 0, 1, 2, 3 and 28. It will be estimated by urine analysis for biomarkers Neutrophil Gelatinase-Associated Lipocalin [NGAL, (69)] and Kidney Injury Molecule-1 [KIM-1, (70)]. These biomarkers will be checked using routine lab procedures at set time points.- Change in fasting parameters will be calculated using blood samples taken on the day before surgery and on the day of surgery. Laboratory values investigated by routine lab procedures are fasting glucose (mmol/L), fasting insulin (pmolU/L), albumin (g/L), IGF-1 (nmol/L), growth hormone (hGH, mU/L), fT4 (pmol/L), reverse-T3 (nmol/L), fT3 (nmol/L), TSH (mE/L) and β-Hydroxybutyrate (mmol/L).- Subject wellbeing will be determined via the PedSQL Cancer Module questionnaire (62, 63) and the internally developed behavior questionnaire. Another internally developed questionnaire will be used to investigate the burden of intervention. These questionnaires will be taken at set time points before surgery, at the end of admission and 1 week after surgery.- Physical activity will be measured via an accelerometer [ActiGraph wgt3x-bt (71)]. Participants will wear the accelerometer in the 7 days before surgery and for another 7 days from postoperative day 4. Open-source software will be used to evaluate physical activity levels during the pre- and postoperative period.- Physiotherapy assessment will be performed twice. This assessment will evaluate (skeletal) muscle mass [leg circumference, quadriceps muscle ultrasonography (65)], body composition (bio-electrical impedance analysis) and gross motor function (GMFM-88) (67). In children who can walk independently for over 6 months, information on physical functioning and strength will be assessed via SARC-F questionnaire (64).- Postoperative hospital admission time will be measured in days since surgery.- Occurrence of peri-operative complications will be carefully assessed. Important complications, such as perioperative tumor spill, hematoma, (wound) infection, intussusception and hypoglycaemia will be investigated and reported in percentages.- Body weight will be assessed regularly during study runtime at set time points. It will be compared between both study groups and between time points (f.i. pre- and post-fasting).- Blood pressure will be assessed regularly during study runtime at set study visits and during hospital admittance. We will collect data on blood pressure (mmHg), presence of hypertension (yes/no) and use of anti-hypertensives (yes/no).- Blood samples and the tissue biopsies obtained will be used to determine upregulation of cytoprotective genes and anti-inflammatory markers associated with the fasting state. Appendix II provides extensive information regarding the histological and molecular analysis. In general, the samples will be used to conduct an expression analysis of genes responsive to fasting, e.g., cytoprotective antioxidant genes, GH/IGF1, and DNA damage and toxicity markers.

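### The blanket statement that investigators cannot be blinded is wider than its reason: the fast does not prevent masking of those who score the observer-dependent secondary outcomes

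*Protocol article*

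**What the plan says.** The Randomization section states, with the nature of the intervention as the reason, that "subjects and investigators cannot be blinded to the result of randomization". It makes no exception for anyone who measures or reads an outcome. The Introduction describes the study as a "single-center, prospective, parallel-group, non-blinded, randomized controlled trial in pediatric patients with renal tumors", and the Abstract and Discussion also call it non-blinded.

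On measurement, Study Procedures lists leg circumference, "ultrasonography of quadriceps muscles using a portable linear transducer" and bio-electrical impedance, and adds that "Motor function will be evaluated using the Gross Motor Function Measure". Under Secondary Outcomes, "Physiotherapy assessment will be performed twice"; the dates of the two visits and the person who performs them are not given. The same section says that every secondary outcome is compared between arms. Statistical Analysis sets a two-sided 0.05 level and names the physiotherapy assessment among the outcomes tested.

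For the laboratory work, "Blood samples and the tissue biopsies obtained will be used to determine upregulation of cytoprotective genes and anti-inflammatory markers". For the primary endpoint, "AKI is defined according to the KDIGO-guidelines (68"), using creatinine from the routine laboratory and urine output from routine clinical recording, on postoperative day 3.

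**The concern.** An open-label intervention does not by itself require open-label assessment. The article moves from the first to the second in one sentence, on a reason that supports only the first. Families know whether the child fasted, and so does the ward. A physiotherapist who scores motor function or holds an ultrasound probe after the operation does not need to know, and neither does a laboratory reader with a coded sample.

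At stake is measurement bias in outcomes that depend on the observer's hand or judgement. The Discussion states the hoped-for direction: less treatment-related toxicity with fasting. An assessor who knows the arm and shares that expectation can shift scores slightly one way. Randomization does not protect against this, and none of the planned adjustments (age, sex, weight, compliance) removes it afterwards.

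**Working it through.** The article gives no figure on this point to reproduce, so the first part of the check sets its statements side by side.

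**Does the stated reason reach the assessors?**
- The fast lasts 10, 14 or 18 hours by age group and takes place before surgery, during the admission that starts the day before (Intervention).
- The visible sign of the arm is a notice on the door while the child fasts (Discussion).
- AKI is assessed 48–72 h after surgery (Primary Outcome).
- Tissue comes from the kidney already removed and is analysed away from the bedside (Study Procedures, Secondary Outcomes).
- Each subject receives a study-ID at inclusion (Confidentiality), so a code for labelling samples already exists.

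Nothing in a completed fast obliges a later rater or a sample reader to know the arm.

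**How exposed is each outcome?**
- GMFM-88, leg circumference, quadriceps ultrasound: scored or acquired by a person, so exposed.
- Gene expression: an assay readout, so little exposed.
- AKI: laboratory creatinine against numeric thresholds, so little exposed. The softer component is urine output, recorded in routine care.
- Parent-completed questionnaires: exposed, but masking an assessor cannot help, because the parent knows the arm.

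**What could a given drift do? (illustration only)**

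Inputs: 50 patients (Sample Size Calculation), read as the total and all analysed; 1:1 allocation (Randomization), hence n = 50 / 2 = 25 per arm; two-sided 5% level, critical value 1.96 (Statistical Analysis). Assumptions not taken from the documents: no true effect, a continuous outcome, a normal approximation, and an assessor drift of d standard deviations in favour of one arm.

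The test statistic is shifted by λ = d × √(n/2) = d × √12.5 = 3.536 d. The rejection rate is Φ(λ − 1.96) + Φ(−λ − 1.96).
- d = 0: λ = 0; rate 0.05, the nominal level.
- d = 0.2: λ = 0.71; 0.105 + 0.004 = 0.109, about 11%.
- d = 0.3: λ = 1.06; 0.184 + 0.001 = 0.186 (0.1855 before rounding of the parts), about 19%.
- d = 0.5: λ = 1.77; 0.424 + 0.000 = 0.424, about 42%.

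The calculation turns an assumed bias into an error rate. It does not show that any such bias will occur.

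**The case against.** The strongest objection is that the article never says that physiotherapists, ultrasound operators or tissue readers will know the arm. It says investigators, not all staff, and a trial labelled non-blinded may still have masked assessors. The article is also a condensation. It refers to Appendix III for procedures and Appendix II for histology and molecular work, and the full protocol is available on request. Instructions to assessors and sample labelling could well be there.

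This stands as far as silence goes: the absence of masking details in an article is no fault. It does not dispose of the point, because the Randomization section makes a positive and unqualified statement of impossibility, with a reason that does not cover its full scope. If the appendices do mask some assessors, that sentence is too broad and should say who is masked.

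A second objection also stands in large part. A reader might infer that the primary endpoint is compromised. The documents do not support that: creatinine is a routine laboratory value and the KDIGO thresholds are numeric. Classifying AKI without the arm variable would protect the classification step only; it cannot correct a urine output charted by ward staff who know the arm. The tissue assays likewise carry little risk.

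Third, feasibility cannot be confirmed from the article. It does not say who performs the physiotherapy assessments, when, or whether the same people give perioperative care at this single centre. That limits how certain one can be that masking will work, but it is no reason to rule it out in advance.

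**Conclusion.** The point holds in a limited form. The reason given justifies leaving families and treating or ward staff unblinded; it does not justify extending this to those who score outcomes after the fast. The avoidable bias lies mainly in three observer-dependent secondary measures: GMFM-88, leg circumference and quadriceps ultrasound. It is small for AKI and for gene expression.

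The size is unknown, since the documents give no basis for a drift. A reader might take the 42% at 0.5 SD as this trial's false-positive risk. It is not: it follows from an assumed drift and applies only to a continuous observer-rated outcome, not to the binary primary endpoint.

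The conclusion assumes that at least one physiotherapy visit follows the fast, which the article does not date, and that the appendices do not already mask these assessors. The change is worth making because it costs little and must be in place before the measurements are taken.

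**What to change.** - In Randomization, limit the statement to children, caregivers and treating staff.
- State that the existing physiotherapy and ultrasound assessor is not told the arm, and that any unblinding is recorded.
- Label tissue and blood samples with the study-ID only.
- As a no-cost safeguard, derive KDIGO status and stage by a fixed rule from creatinine and urine output without the arm variable, and acknowledge that this does not protect the charting of urine output.
- If the appendices already provide for any of this, say so in the main text.

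The cost is instructions and labels, with no new procedure and no added burden for the child. It presumes that the assessor is not also involved in the fasting care, which the centre must check. The drawback is that masking will sometimes fail when a family mentions the fast; recording these cases shows how often.
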